### Outcome measures and time points

2.7

#### General assessments

2.7.1

Demographic and medical history data, including height, weight, sex, age, BMI, prior cholecystectomy, duration of diabetes, current glucose-lowering regimen, comorbid treatments, alcohol/smoking history, allergy history, and family history, will be collected at baseline. These data will be used to control for confounders and perform subgroup analyses.

#### Primary efficacy outcome and assessment time points

2.7.2

The primary efficacy endpoint is the total score of the Metformin Symptom Severity Score, a validated, widely used self-report tool originally developed and psychometrically validated by McCreight et al. specifically for evaluating metformin-related gastrointestinal intolerance in adults with T2DM (McCreight et al., 2018).

In the original validation study by McCreight et al., this questionnaire demonstrated excellent reliability and validity: it showed strong internal consistency (Cronbach's α > 0.8), good test-retest reliability, and significant discriminant validity, with a highly significant difference in total scores between metformin-intolerant and metformin-tolerant patients (*P* < 0.0001) (McCreight et al., 2018). The questionnaire covers medication adherence, reasons for discontinuation, dose tolerance, gastrointestinal symptoms (nausea, abdominal bloating/pain, and diarrhea; frequency and subjective severity), changes in baseline symptoms, and an overall subjective tolerance rating, with a total score ranging from 0 to 50 points (0–10 = tolerable, 11–20 = mild intolerance, 21–30 = intolerable, 31–50 = severe intolerance). This questionnaire is used for the quantitative assessment of intolerance-related symptoms in this trial, not as a basis for clinical diagnosis.

Assessment time points include baseline, Week 2, and Week 4. Details of the questionnaire items and scoring criteria are provided in Table 2 (McCreight et al., 2018).

**Table 2 T2:** The metformin symptom severity score questionnaire.

No	Question	Option	Score
1	Are you still taking metformin?	Yes (skip to question 6)	0
		No	5
2	If you have stopped taking metformin, was it due to side effects?	Yes (continue to question 3)	5
		No (skip to question 6)	0
3	What dose were you taking at the time of discontinuing metformin?	500 mg once daily (1 tablet)	4
		1,000 mg once daily (2 tablets)	3
		500 mg twice daily (2 tablets)	2
		2,000 mg once daily (4 tablets)	1
		1,000 mg twice daily (2 tablets)	0
4	Have you ever taken a lower dose of metformin and tolerated it well?	Yes	0
		No	1
	If yes, what was the maximum dose you tolerated?	(e.g., 500 mg once daily)	2
5	Have you been trialed on a modified release preparation of metformin (e.g. Glucophage SR)?	Yes	2
		No	0
In the last week of taking metformin, have you experienced?			
6	Nausea?	Yes	1
		No	0
	If yes, how often?	More than once a day	4
		Once a day	3
		Occasionally	2
		Only once	1
	How would you score its severity from 1 to 5 (where 1 is mild, not causing distress or affecting your daily routine, and 5 is very severe, causing marked distress and/or disrupting your daily activities)?	_______/5	
7	Abdominal bloating/pain?	Yes	1
		No	0
	If yes, how often?	More than once a day	4
		Once a day	3
		Occasionally	2
		Only once	1
	How would you score its severity from 1 to 5 (where 1 is mild, not causing distress or affecting your daily routine, and 5 is very severe, causing marked distress and/or disrupting your daily activities)?	_______/5	
8	Diarrhea?	Yes	1
		No	0
	If yes, how often?	More than once a day	4
		Once a day	3
		Occasionally	2
		Only once	1
	How would you score its severity from 1 to 5 (where 1 is mild, not causing distress or affecting your daily routine, and 5 is very severe, causing marked distress and/or disrupting your daily activities)?	_______/5	
9	Have you experienced any of the side-effects you have described above PRIOR to starting metformin?	Yes	−5
		No	0
	If yes, whilst taking metformin have the symptoms:	Improved	−1
		Worsened	1
		Stayed the same	0
10	Would you describe yourself as:	Tolerant of metformin treatment	0
		Mildly intolerant of metformin treatment	1
		Intolerant of metformin treatment	2
		Severely intolerant of metformin treatment.	3
For clinical staff only			
No	Item	Record	
1	Total score (0–50)	____/50	
2	Tolerability rating	(T/MI/I/SI)	
3	Patient-reported tolerability	(T/MI/I/SI)	
4	Correlation	(Y/N)	
Scoring criteria			
No	Total score range:	Record	
1	0–10: (tolerant, *T*)		
2	11–20: (mildly intolerant, MI)		
3	21–30: (intolerant, I)		
4	31–50: (severely intolerant, SI)		

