#### Diagnostic criteria for metformin intolerance

2.3.2

Metformin intolerance will be defined as meeting any of the following criteria (McCreight et al., 2018):

(1) Prior use of metformin with treatment discontinuation due to gastrointestinal intolerance (prior exposure ≤ 1,000 mg/day for ≤ 8 weeks); or(2) Inadequate glycaemic control [e.g., HbA1c ≥ 7.0% (53 mmol/mol)] with inability to escalate metformin to ≥500 mg/day because of intolerable gastrointestinal symptoms.

(Reference tolerability: individuals taking divided doses of metformin up to 2,000 mg/day without clinically significant gastrointestinal adverse effects.) Other causes of diarrhea must be excluded before confirming the diagnosis (McCreight et al., 2018).

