### Interventions

2.6

This is a parallel-group trial employing a “standard care + targeted intervention” design. Both groups will receive standardized diabetes management and metformin therapy as background treatment; in addition, participants will receive either taVNS or sham control group. The treatment course for both arms is 2 weeks, with subsequent follow-up assessments.

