#### Standard care (background therapy)

2.6.1

Background therapy follows international guideline recommendations and comprises standardized lifestyle counseling and medication management. Lifestyle counseling includes: dietary guidance with carbohydrates accounting for 45–60% of total daily energy intake and dietary fiber ≥25 g/day; at least 150 min/week of moderate-intensity aerobic activity (for example, brisk walking or cycling); and standardized education on disease management, medication adherence, and management of gastrointestinal symptoms to ensure consistency across participants (American Diabetes Association, 2024a,b).

Medication management principles are as follows:

Discontinue or avoid medications known to exacerbate gastrointestinal symptoms where clinically appropriate (e.g., stimulant laxatives or certain over-the-counter preparations);

In participants with inadequate glycaemic control, additional antihyperglycaemic agents (for example, SGLT2 inhibitors or DPP-4 inhibitors) may be added as clinically indicated, provided such additions are unlikely to aggravate gastrointestinal function; adjustments will follow current guideline recommendations and be documented;

Concomitant treatment for chronic conditions (e.g., antihypertensives for hypertension or secondary prevention therapies for coronary artery disease) will be maintained but clinicians should avoid introducing agents known to provoke GI intolerance when alternatives are available.

Metformin dosing will follow a “start low, escalate gradually” regimen: initial dose 500 mg administered with meals twice daily; dose titration will proceed weekly guided by fasting blood glucose (target 4.4–7.0 mmol/L), with a maximum dose up to 2,000 mg/day or the participant's maximal tolerated dose. Dose adjustments and all concomitant medications will be supervised and recorded by study physicians. In the event of severe, poorly tolerated diarrhea (e.g., ≥5 bowel motions per day with clinical signs of dehydration), metformin will be withheld or adjusted and symptomatic therapy provided (e.g., diosmectite); severe events will be managed according to the study Serious Adverse Event (SAE)—defined per the Common Terminology Criteria for Adverse Events (CTCAE) as any adverse event resulting in death, life-threatening illness, hospitalization, persistent disability, or requiring immediate emergency intervention—procedure and continue to be followed up (Rena et al., 2013).

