##### Bowel urgency

2.7.3.2

Bowel urgency reflects the temporal urgency for defecation following medication. The shortest daily response interval is recorded and quantified on a 0–3 scale: 0 = no urge/>3 h, 1 = ≤ 3 h, 2 = ≤ 2 h, 3 = ≤ 1 h. Assessment time points are baseline, Week 2, and Week 4.

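### The primary score's symptom items refer to the last week on metformin, so for anyone off the drug at a visit they describe a past week, possibly one before stimulation

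*Protocol article*

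**What the plan says.** Section 2.7.2 of the protocol article defines the outcome: "The primary efficacy endpoint is the total score of the Metformin Symptom Severity Score". On timing it says: "Assessment time points include baseline, Week 2, and Week 4".

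Table 2 prints the form. Items 6–8 (nausea, bloating or pain, diarrhoea) share the lead-in "In the last week of taking metformin, have you experienced". Nothing in the article replaces it with a calendar window tied to the visit.

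People off the drug still reach these items. Someone who answers No at item 1 goes to item 2, "If you have stopped taking metformin, was it due to side effects", and from there to item 6, either directly or through items 3–5.

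Four other sections bear on who may be off metformin, and when:

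- Section 2.3.2, criterion (1), admits people with "Prior use of metformin with treatment discontinuation due to gastrointestinal intolerance". It sets no limit on how long ago they stopped.
- Section 2.6 states: "Both groups will receive standardized diabetes management and metformin therapy as background treatment". Section 2.6.1 describes a low starting dose with weekly titration, but gives no start day relative to the baseline questionnaire.
- Section 2.6.1 also provides that, in severe diarrhoea, "metformin will be withheld or adjusted and symptomatic therapy provided (e.g., diosmectite". Section 2.8.2 provides for discontinuation in severe complications.
- Section 2.6.5 sets a baseline period of Week −1 to 0 and does not say whether it is spent on or off metformin.

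**The concern.** A repeated outcome should describe the period that each visit stands for. Here the look-back of the symptom block follows drug exposure instead of the visit date, with two consequences.

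**Baseline.** If a criterion (1) participant has not restarted when the form is completed, the symptom block is a memory of the week before they stopped. Once metformin is restarted, Week 2 scores the current week. The same person's baseline stool diary (2.7.3.1) would come from an off-drug week. Section 2.7.3.2 says "Bowel urgency reflects the temporal urgency for defecation following medication", and if the medication meant is metformin, there is no dose to count from. The baseline symptom score and baseline bowel measures would then cover different periods.

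**Follow-up.** A participant who stops early in treatment and does not resume is asked about one and the same week at Week 2 and at Week 4. That block cannot reflect stimulation given after the stop.

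At stake are the pilot's main products: the SD of this total score (2.4) and the effect-size estimates named in the abstract. The multiple imputation in 2.10 does not help, because the score is present, not missing. Current-week symptoms that were never asked about cannot be recovered later.

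**Working it through.** **The plan's own figures.** Section 2.4: 30 × (1 − 0.15) = 25.5, taken as 25 evaluable per group; 2 × 25 − 2 = 48 degrees of freedom. These reproduce, and this point disputes none of them.

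**Points tied to the recall window (Table 2).** Each symptom scores 1 for presence, up to 4 for frequency and up to 5 for severity. Items 6–8 therefore carry 3 × (1 + 4 + 5) = 30, and 30/50 = 60% of the nominal total. A participant on metformin skips items 1–5, so the attainable maximum is 30 + 3 (item 10) = 33, of which items 6–8 are 30.

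**Points not tied to it.** For someone who stopped because of side effects, items 1–5 give at least 5 + 5 = 10 and at most 5 + 5 + 4 + 2 + 2 = 18. For someone on the drug they give 0. The total therefore still moves when a participant stops or restarts.

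**Week described after a stop on Day d with no resumption.** The window is Day d − 7 to Day d. The lag from its end is 14 − d days at Week 2 and 28 − d days at Week 4 (nominal visit days).

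| Stop day | Week described at both visits | Days before stimulation | Lag at Week 2 | Lag at Week 4 |
|---|---|---|---|---|
| 0 | −7 to 0 | 7 | 14 | 28 |
| 2 | −5 to 2 | 5 | 12 | 26 |
| 5 | −2 to 5 | 2 | 9 | 23 |
| 7 | 0 to 7 | 0 | 7 | 21 |
| 10 | 3 to 10 | 0 | 4 | 18 |

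The window lies wholly before stimulation only for a stop at about Day 0. Stops on Days 1–6 straddle the start.

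**Size of a recall shift (hypothetical answers).** Nausea and diarrhoea recalled as once daily at severity 4 score 2 × (1 + 3 + 4) = 16. The same two symptoms now, occasional at severity 2, score 2 × (1 + 2 + 2) = 10. The difference of 6 points arises with no treatment effect.

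**Size of dilution (assumed share).** The documents give no rate. Suppose a share f, equal in both arms, has symptom answers that cannot respond to stimulation, and the SD is unchanged. The mean effect on items 6–8 is multiplied by (1 − f), and the n needed in a later trial for equal power on those items by 1/(1 − f)².

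| f | Effect kept | n multiplier |
|---|---|---|
| 5% | 95% | 1.11 |
| 10% | 90% | 1.23 |
| 20% | 80% | 1.56 |
| 30% | 70% | 2.04 |

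**The case against.** **Baseline may be on-drug.** Section 2.10 lists baseline metformin dose as an imputation covariate, 2.3.3 requires a stable antihyperglycaemic regimen before baseline, and urgency after medication is scheduled at baseline. These hints stand, and they make the baseline part conditional. They do not settle it: a baseline dose can be zero, 2.6.1 speaks of an initial dose, and a stable regimen sits poorly with a restart just before baseline.

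**Randomisation.** A reader might infer that the recall contrast creates an apparent benefit of taVNS. The documents do not support that. The trial is randomised and sham-controlled, the model in 2.10 contains group, time and their interaction, and a baseline shift is balanced between arms in expectation. What remains is added variance and an unreliable within-arm change. A later trial with the same form and the same mix of participants would share this SD, but the estimate would not carry over if the mix or the wording changed.

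**Follow-up cases are few.** The problem needs an early stop without resumption. Under a dose adjustment or an extended-release switch the participant stays on the drug and the window stays current. This stands, and no frequency is given.

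**The total still responds.** A reader might also infer that the outcome stops responding altogether in those who stop. It does not: items 1–5 add at least 10 points for a stop due to side effects, and item 10 can change. Only the symptom block is fixed to one week, and even there the recalled answers need not be identical at the two visits.

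**Validated wording.** Changing the lead-in departs from an instrument that the protocol relies on as validated. That is a reason to keep the source instrument's wording alongside. The discriminant evidence described in 2.7.2 separates tolerant from intolerant patients; no evidence of responsiveness to change is described.

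**Conclusion.** The point holds in a conditional form. As printed, 30 of the nominal 50 points can describe a past week at any of the three visits for a participant who is off metformin then. At baseline this requires that a criterion (1) participant has not restarted before the form is completed, which the article leaves open. At Weeks 2 and 4 it requires an early stop without resumption. Participants on metformin at a visit are unaffected.

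The consequence is extra variance, unreliable within-arm change, and a symptom block that cannot reflect later stimulation in those who stop for good. The overall size cannot be fixed from the documents. The dilution figures rest on an assumed share, equal in both arms, and concern items 6–8 only. If stopping differed by arm, the direction of the distortion would not be determined. The 6-point example shows scale only. Nor do the documents support calling the recalled week the worst one: the item asks for the last week on the drug. The matter deserves correction because it sits in the wording of the primary instrument and the remedy is cheap.

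**What to change.** 1. Reconcile 2.3.2, 2.6.1 and 2.6.5 on whether participants are on or off metformin in the Week −1 to 0 baseline week, so that symptom score, stool diary and urgency refer to the same week. Which it should be is for the investigators.
2. At Baseline, Week 2 and Week 4, ask items 6–8 for the past 7 days. On the same form record the date of the last metformin dose and whether metformin was taken in those 7 days.
3. Keep the score as worded in the source instrument alongside, for comparability with it, and state in 2.7.2 which of the two totals is primary.
4. Report the 7-day symptom scores by on/off-metformin status, and treat stopping metformin as a separately reported intercurrent event.

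Step 4 is needed because replacing the lead-in alone would bring a new artefact. Off the drug, a 7-day score may fall simply because metformin was stopped, and it may rise on restarting. Without the exposure record, the first could be read as benefit and the second as harm.

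The cost is three repeated items, a short metformin exposure entry, and a 7-day version that departs from the source wording. Answers of participants continuously on metformin are essentially unchanged, and the stated sample size is not affected.

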#### Secondary efficacy outcomes and assessment time points

2.7.3

Secondary outcomes include stool characteristics, bowel urgency, glucose and insulin metabolism parameters, inflammatory cytokines, and gastrointestinal function markers. Sample collection follows SOPs. Blood samples ≥3 ml are aliquoted, stored short-term at 4 °C, and long-term at −80 °C, with strict adherence to kit instructions and quality control procedures.

##### Bristol stool form scale (BSFS)

2.7.3.1

Stool form is evaluated using the Bristol Stool Form Scale. Participants record daily bowel movements, noting type (1–7). Weekly average stool scores are calculated to assess diarrhea incidence. If multiple types occur on the same day, the highest score is recorded. Assessment time points are baseline, Week 2, and Week 4. See Figure 3 for illustrative diagram and Table 3 for scoring criteria.

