**Figure 3 F3:**
[figure not shown]
Bristol stool form classification diagram.

**Table 3 T3:** Bristol stool form classification scoring table.

Type	Form	Score
1	Separate hard lumps, like nuts, difficult to pass	1
2	Sausage-shaped but lumpy	2
3	Sausage-shaped with cracks on surface	3
4	Sausage or snake-shaped, smooth and soft	4
5	Soft blobs with clear edges, easy to pass	5
6	Fluffy pieces with ragged edges, mushy	6
7	Watery, no solid pieces	7

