### Statistical methods

2.10

All data will be managed according to GCP guidelines for clinical trials. Two independent researchers will perform double data entry for all variables, including bowel urgency scores, glucose and insulin metabolism markers, serum inflammatory markers, and safety parameters. Cross-verification is mandatory, and the database will be locked without authorization.

Statistical analyses will be performed by blinded biostatisticians using SAS 9.4 and R 4.2.1. Two analysis sets will be applied: the intention-to-treat (ITT) set includes all randomized participants, and the per-protocol (PP) set includes participants completing ≥80% of the treatment course without major protocol violations, for sensitivity analysis.

Baseline characteristics will be summarized by group. Continuous variables are assessed for normality using the Shapiro–Wilk test: normally distributed variables are presented as mean ± SD, non-normal as median [IQR]; variance homogeneity is assessed via Levene's test. Categorical variables are expressed as counts (*n*) and percentages (%). Between-group comparisons: independent *t*-test or Mann–Whitney *U*-test for continuous variables, Pearson χ^2^ or Fisher's exact test for categorical variables.

Primary and continuous outcome variables (bowel urgency score, FBG, PG2h, FINS, C-peptide, HOMA-IR, ISI, GA, serum IL-6/IL-10/TNF-α, GLP-1, 5-HT, D-lactate, diamine oxidase, and fecal bile acids) will be analyzed using linear mixed-effects models (fixed effects: group, time, interaction; random effect: participant), reporting least-squares means with 95% *CI*. The exact mathematical formulas and covariance structures for these linear mixed-effects models will be fully reported in the final trial publication. Categorical outcomes are analyzed via χ^2^ or Fisher's exact test.

A Multiple Imputation (MI) model will be used as the primary method for missing data. The imputation model will include all primary and secondary outcomes, plus baseline covariates (age, sex, duration of diabetes, baseline metformin dose, baseline Metformin Symptom Severity Score score), with 20 Markov Chain Monte Carlo iterations to generate 20 imputed datasets. The pre-specified linear mixed-effects model will be performed on each dataset, with results pooled via Rubin's rules (Heymans and Twisk, 2022).

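### The weekly mean Bristol score is used to assess diarrhoea incidence, but a mean of stool form does not determine the number of diarrhoea days

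*Protocol article*

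**What the plan says.** Section 2.7.3.1 has participants note the Bristol type of their bowel movements each day. It sets a rule within the day: "If multiple types occur on the same day, the highest score is recorded". It then names the weekly summary and its purpose together: "Weekly average stool scores are calculated to assess diarrhea incidence". The time points are baseline, Week 2 and Week 4.

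Table 3 places form on a single line. Score 1 is "Separate hard lumps, like nuts, difficult to pass", score 4 is smooth, soft and formed, score 6 is "Fluffy pieces with ragged edges, mushy" and score 7 is "Watery, no solid pieces". Neither Table 3 nor section 2.7.3.1 says which types count as diarrhoea, or what weekly mean would do so.

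Section 2.6.5 groups the Bristol scale with the primary and key secondary outcomes. Section 2.10 gives mixed models for continuous outcomes, in a list that does not name the Bristol score, and adds: "Categorical outcomes are analyzed via χ^2^ or Fisher's exact test".

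**The concern.** The measure and its stated purpose do not match. Incidence counts events: diarrhoea days, or participants with at least one. The weekly mean is an average consistency. Two participants with the same mean can have had different numbers of diarrhoea days, and the one with more can have the lower mean.

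This is a stated rule that does not deliver what it is said to deliver. An analysis plan that followed the sentence would carry the mismatch forward.

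Diarrhoea is one of the three symptoms in the primary score, and the abstract says the pilot is to supply effect-size estimates for later confirmatory trials. A difference in mean form reported as a difference in diarrhoea incidence would be a poor basis for that later design.

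**Working it through.** The protocol gives no figure to reproduce here, so the check is whether the weekly mean determines the number of diarrhoea days.

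**Inputs.** Daily score 1–7, the highest of the day (section 2.7.3.1 and Table 3); seven recorded days per week; weekly mean = sum of daily scores / 7. Assumption, not in the document: a diarrhoea day is type 6 or 7. Other cut-offs are tried below.

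**Step 1: weeks without hard stools.**

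| Week | Mean | Days of type 6–7 | Days of type 7 |
|---|---|---|---|
| 7,7,4,4,4,4,4 | 34/7 = 4.86 | 2 | 2 |
| 5,5,5,5,5,5,5 | 35/7 = 5.00 | 0 | 0 |
| 7,7,5,4,4,4,4 | 35/7 = 5.00 | 2 | 2 |

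The first week has two watery days and a lower mean than the second, which has none. The second and third have the same mean and differ by two days. Dilution by formed or soft days is enough to produce this.

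**Step 2: weeks with hard stools.**

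| Week | Mean | Days of type 6–7 | Days of type 7 |
|---|---|---|---|
| 4,4,4,4,4,4,4 | 28/7 = 4.00 | 0 | 0 |
| 7,7,7,2,2,2,2 | 29/7 = 4.14 | 3 | 3 |
| 7,7,7,1,1,1,4 | 28/7 = 4.00 | 3 | 3 |

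Here hard-stool days offset watery days, and almost the same or the same mean goes with zero or three diarrhoea days.

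**Step 3: all possible seven-day weeks.** For a given mean, the range of days with type 6 or 7 is:

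| Scores allowed | Mean 4.00 | Mean 5.00 | Mean 6.00 |
|---|---|---|---|
| 1–7 | 0 to 4 | 0 to 5 | 4 to 7 |
| 3–7 | 0 to 2 | 0 to 4 | 4 to 7 |
| 4–7 | 0 to 0 | 0 to 3 | 4 to 7 |

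The mean is informative when it is high: at 6.00 at least four days must be type 6 or 7. Around 5.00 it leaves the count open even with no score below 4.

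**Step 4: other cut-offs.** With type 7 alone, the contrasts in Steps 1 and 2 are unchanged (last column). With type 5 or above, the type-5 week would itself be seven diarrhoea days, so the ranking in Step 1 no longer illustrates the problem, but another pair does: 7,7,4,4,4,4,4 and 5,5,5,5,5,5,4 both sum to 34 (mean 4.86) and have 2 and 6 such days. The mean does not fix the count at any of these three cut-offs.

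**The case against.** The construct that the section opens with is stool form, and a weekly mean is a usable summary of form. Diarrhoea incidence appears only as a purpose clause; no endpoint of that name is in Table 1 or section 2.10. That stands, and it is why the mean can be kept as a description of form. The sentence still names a purpose that the mean does not serve.

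The mean might be meant to classify each participant's week as diarrhoeal or not, with the categorical tests of section 2.10 applied to the result. The text does not say so, and a cut-off on the mean would inherit the problem: with a threshold of 5.00, the type-5 week is classed as diarrhoeal and the week 7,7,4,4,4,4,4 is not.

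Item 8 of the primary questionnaire asks about diarrhoea directly (presence, frequency, severity), so a reader should not infer that the trial fails to measure it. But item 8 is a recalled item with coarse frequency bands, summed into a total, and section 2.7.3.1 does not refer to it.

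A reader might also infer that the defect lies in hard-stool days cancelling watery ones. The document does not support that as the main mechanism. The highest-of-the-day rule removes cancellation within a day, so it takes whole days whose loosest stool is hard, in the same week as watery days, and nothing suggests that this is common here. The point does not depend on it (Step 1).

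**Conclusion.** The point holds in a limited form. The weekly mean does not determine the number of diarrhoea days, so it does not measure what section 2.7.3.1 says it is for. At a mean of 5.00 the count can be anything from 0 to 5 days, or 0 to 3 when no score is below 4. These counts assume that types 6–7 are diarrhoea; the conclusion also holds for type 7 alone and for type 5 or above.

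A reader might go further and conclude that a treatment effect on diarrhoea would vanish or reverse. That is not shown. The examples are single constructed weeks, not arm comparisons, and a high mean does imply many loose days. What can be said is that the measure could misstate a difference between arms, by an amount that the document does not allow one to estimate.

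The weight is moderate: this is a secondary outcome in a pilot for which section 2.4 plans no formal efficacy testing, and the daily records needed for the repair are already collected. It should be corrected before the result is reported as an incidence.

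**What to change.** Change section 2.7.3.1, or the analysis plan, so that diarrhoea incidence is derived from the daily diary:

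- Prespecify the Bristol cut-off for a diarrhoea day, applied to the highest type of the day that is already recorded. Type 6 or above is one example, with type 7 alone as a sensitivity check; the choice is the sponsor's.
- For each participant and assessment week, derive the number of days at or above the cut-off, or their proportion among recorded days so that incomplete diaries can be used.
- Report this by arm, with the between-arm difference and its 95% CI, as the diarrhoea-incidence measure.
- Keep the weekly mean, described only as a summary of stool form.

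The cost is one derived variable and about one sentence of text. It needs no new data and adds no burden for participants.
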